# Clinical investigation plan for the use of interactive binocular treatment (I-BiT) for the management of anisometropic, strabismic and mixed amblyopia in children aged 3.5–12 years: a randomised controlled trial

**DOI:** 10.1186/s13063-019-3523-0

**Published:** 2019-07-16

**Keywords:** Amblyopia, I-BiT™, Randomised clinical trial, Lazy eye, Child

## Abstract

**Background:**

Amblyopia (lazy eye) affects the vision of approximately 2% of all children. Traditional treatment consists of wearing a patch over their ‘good’ eye for a number of hours daily, over several months. This treatment is unpopular and compliance is often low. Therefore, results can be poor. I-BiT is a system, based on stereo technology using shutter glasses, designed to treat amblyopia using dichoptic stimulation. This trial uses a redesigned system for home use and includes eye-tracking capability.

**Methods/design:**

This is a randomised controlled trial involving three groups of 40 patients each, aged between 3.5 and 12 years, with a diagnosis of (1) anisometropic amblyopia, (2) mixed or strabismic amblyopia prior to strabismic surgery and (3) mixed or strabismic amblyopia who have just undergone strabismus surgery. They will be randomised in a 1:1 ratio between I-BiT and control and will receive treatment, at home over a 6-week period. Their visual acuity will be assessed independently at baseline, mid-treatment (week 3), at the end of treatment (week 6) and, for those receiving the active I-BiT treatment, 4 weeks after completing treatment (week 10).

The primary endpoint will be the change in visual acuity from baseline to the end of treatment. Secondary endpoints will be additional visual acuity measures, patient acceptability, compliance and the incidence of adverse events.

**Discussion:**

This is a randomised controlled trial using the redesigned I-BiT™ system to determine if this is a feasible treatment strategy for the management of anisometropic, strabismic and mixed amblyopia.

**Trial registration:**

ISRCTN Number/Clinical trials.gov, ID: NCT02810847. Registered on 23 June 2016.

**Electronic supplementary material:**

The online version of this article (10.1186/s13063-019-3523-0) contains supplementary material, which is available to authorized users.

## Background

The term amblyopia is derived from the Greek, meaning blunted sight and is defined as a unilateral or bilateral decrease in vision for which no obvious cause can be found on clinical examination, or as von Graefe phrased it, a condition where the observer sees nothing and the patient very little [1]. It is a common condition affecting 2–3% of the population [2].

Amblyopia is characterised by:-Reduced visual acuityThe phenomenon of crowdingPresence of a central suppression scotomaImpairment of binocular vision

Von Graefe was the first to demonstrate suppression in a lazy eye [3] and there is evidence of suppression in all amblyopes [4].

The first-line treatment is the correction of any existing significant refractive error for at least 18 weeks (refractive adaptation) but full resolution only occurs in about 30% [5, 6]. For patients in whom the amblyopia persists, then the mainstay of treatment has been patching, or more recently, penalisation. The major barrier to patching is that wearing patches is uncomfortable and accordingly compliance is variable. Objective measurements suggests that average concordance with patching was 48% [7]. A major factor may well be the association of increased reports of bullying by children who wear patches [8].

The second issue is that the normal eye is covered up. Accordingly, while it may improve the vision in the amblyopic eye, it can lead to reduced vision in the patched eye and there is still the outstanding issue of developing stereopsis.

An alternative treatment is to use a strategy based on dichoptic stimulation [9]. Dichoptic stimulation is the ability to present different images to each eye independently. For example, one could present the sprite (a sprite is a computer graphic which may be moved on-screen and otherwise manipulated as a single entity and here refers to a gaming object of interest) to one eye and objects to collect to the other eye thereby forcing both eyes to work together in order to successfully play the game. The I-BiT group, who were one of the first to adopt this approach, did so using a variation on the game Nux.

There is nothing original in the idea and a number of devices had been developed, starting with Priestly-Smith’s fusion tubes followed by Worth’s amblyoscope and then by the 1930s Maddox developed the major amblyoscope, or synoptophore. The synoptophore allows such tasks as putting the lion (seen by one eye) in the cage (seen by the other) and was developed very much with the idea of dichoptic stimulation for therapeutic benefit. However, such tasks were too simple to retain anyone’s interest beyond a few minutes and way short of the hours needed for any therapeutic effect.

What has changed is the rapid advances in stereo-viewing technology that has given this approach a new lease of life as it can be readily adapted for dichoptic stimulation. These considerations led us to the initial development of a virtual reality-based system [10] to treat amblyopia using dichoptic stimulation, either playing special video games or watching DVDs which we called I-BiT (*I*nteractive *Bi*nocular *T*reatment). Three pilot studies [11–13] have shown that the I-BiT™ system can improve the visual acuity in amblyopic patients. The most recent of these pilot studies using shutter-glasses technology [13] showed that all patients who completed their planned treatment (nine of the 10 patients) showed a mean improvement in visual acuity of 0.18 LogMAR. This system went to a randomised control trial (RCT) and while all the arms showed a visual improvement of 0.07 LogMAR units, there was no difference between the arms including the control (playing the videogame under non-dichoptic conditions) [14].

A group from Iran developed their own system, which they also called I-BiT but was developed independently of the Nottingham team, using dichoptic games (Pacman, Tetris and Snake) with red-green anaglyph glasses, to treat 50 patients aged 3–10 years old and again showed improvement in vision in both the I-BiT and the control arms [15] but both arms also received patching making the results hard to interpret.

The I-BiT™ system was designed for treating patients under supervision in a hospital-based setting and this significantly limits treatment times to only a few hours (3 h in the trial). There was also no attempt to ‘balance’ the images. The extra visual features that were shown to the amblyopic eye were ‘all or none’.

We have redesigned our I-BiT system for home use along with incorporation of an eye-tracker. The innovation is the combination of the two technologies of virtual reality and eye-tracking. This allows one to achieve the dual aims of dichoptic stimulation and harmonious retinal presentation with engaging visual material that will retain a child’s attention for prolonged periods of time. This combination is currently untested.

This study will aim to evaluate the new system in participants aged 3.5 to 12 years with anisometropic, mixed and strabismic amblyopia.

## Methods/design

### Objectives of the study

The trial is a feasibility study (similar to a stage 2 CTIMP trial) with the aim to show that this treatment strategy is feasible (equipment can be delivered and retrieved from patients’ homes and will function in a home setting) and to get some indication of clinical efficacy as to whether I-BiT combined with refractive correction is superior to refractive correction alone in the treatment of amblyopia in three scenarios (untreated anisometropic amblyopia, mixed or strabismic amblyopia and residual amblyopia in patients undergoing strabismus surgery).

### I-BiT™ system

The redesigned I-BiT system consists of desktop personal computer with a core 5i processor and graphics card and a 27″ HD screen. Attached to the inferior border of the screen is an eye-tracker bar with an infra-red light source. Dichoptic stimulation is achieved by using radio-wave controlled 3D active shutter glasses and a USB controller/infra-red emitter. The infra-red signal is converted to a radiofrequency signal (2.48 GigaHz) in a box which is opaque to infrared and transparent to radio waves. The active shutter glasses are to be worn by the patient as this is the means by which different images are presented to each eye. The controller/radiofrequency emitter synchronizes the glasses with the monitor so that each frame is displayed to the correct eye.

There is a games controller by which the options are selected and the games are played.

The system has the ability to perform simple psychophysical measurements (visual acuity, cover test and test for double vision). The visual acuity is measured using an illiterate E test. The cover test uses the eye-tracker and the target is shown first to the good eye, then to both and then to the amblyopic eye and the movement of the eyes is recorded when the target is switched from appearing to both eyes and is only shown to the amblyopic eye only. The test for double vision is when a bunny rabbit is shown to both eyes and the child is asked to select whether they see one rabbit or two.

It has the ability to off-set the images so as to ensure harmonious retinal presentation of images for patients with strabismic or mixed amblyopia.

### Video stimulus

I-BiT has episodes from popular young children’s programmes (with permission from the British Broadcasting Cooperation). For three of these programmes, there is a blurred patch that is presented to the central vision of the good eye and centrality is maintained by eye-tracking. For the fourth programme and software is used to detect the presence of faces in the images and then the faces that are shown to the good eye are specifically blurred but not for the amblyopic eye. The rationale is that faces have high salience.

### Games stimulus

Eight games have been programmed and they are designed to address different aspects of amblyopia:Two shooter games which have an anti-crowding strategy (based on Nux and Space Invaders)A chaser game which has an anti-suppression strategyA game based on Pac-Man which also has an anti-suppression strategyTwo games that require accurate foveation of the eye (one is based on the arcade game Whack-A-Mole)Two games designed to stimulate binocularity and stereopsis

### Trial design

The trial protocol is version 1.4 and dated 19 December 2016. The trial is a single-masked, randomised control trial. It is not possible to mask the intervention as the participant has only to shut one eye to know whether they are in the treatment or the control arm.

The trial is split into three groups each of these three groups will investigate a distinct (and mutually exclusive) patient population which together cover most cases of anisometropic or strabismic amblyopia that presents to the National Health Service:Group 1: untreated anisometropic amblyopia.Group 2: strabismic or mixed amblyopia with no previous strabismus surgery (but may have had previous amblyopia treatment)Group 3: immediate post-strabismus surgery. Participants with residual strabismic or mixed amblyopia undergoing alignment surgery. These participants will receive I-BiT Plus treatment starting in the immediate post-operative period

The trial will be assessor masked (it is not possible to mask the intervention) randomised intervention with 40 participants in each group with either continued refractive adaptation (if glasses are indicated and prescribed) or observation as the controls. The participants in the control arm will also be provided with a gaming computer on which they can play games and watch DVDs but will not have the capability to provide dichoptic stimulation nor provide eye-tracking. Carers will be provided with a contact number for enquiries and technical help.

In all three groups, the participants will be randomised to either receive I-BiT Plus for 6 weeks or extended refractive adaptation/observation and will be examined at weeks 3 and 6 post receipt of I-BiT Plus or laptop for both arms, and at week 10 in the I-BiT treatment arm only. In all three groups, after week 6, the participants in the control arms will be returned to standard NHS care while the intervention arms will be observed for a further 4 weeks. The rationale is that the week-6 visit is the comparison between treated and controls and is the primary endpoint. The point of the week 10 visit is to see if any improvement observed in the treated arm is stable or not and the comparison is, therefore, between the week-6 and the week-10 visits for the treated arms.

The choice of untreated controls was chosen as the most suitable choice for determining whether I-BiT is an effective treatment and superior to no treatment.

The basic study design is the same for all three groups and is summarised in Fig. 1.

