A second issue arises specifically for strabismic and mixed amblyopia. Only the fovea can support normal visual acuity and so it seems an important requirement that the dichoptic images are presented harmoniously. The revised I-BiT has this capability to off-set images by a required amount and it can measure the distance of the participant from the screen in real time to ensure that the angle of off-set can change with distance such that the degree of off-set as measured in prism dioptres is kept constant. This is a novel development.

We have chosen controls whose only treatment is the wearing of glasses, if indicated rather than patching. To use participants who are under-going patching or penalisation as controls would have made this a non-inferiority study and this requires an infeasibly large number of participants to generate a meaningfully powered study.

All participants, if they have significant refractive error, must have undergone at least 12 weeks of refractive adaptation. Refractive adaptation can occur over 30 weeks [5, 6] and it is standard practice to allow 18 weeks of refractive adaptation before considering patching or penalisation. By allowing enrolment at 12 weeks, it means that the controls can complete their participation in this study and be finished by 18 weeks and so this would not delay the start of conventional treatment, if indicated. It does mean that we anticipate some improvement in vision in the control arms.

The chosen method, described under trial procedures, of how to measure visual acuity was developed following a Delphi-like process involving all the paediatric ophthalmologists and orthoptists at the four participating trial centres. Although the tests are standard, it transpired that there was considerable variation on how these tests are applied in practice. It has been emphasised to all the trial centres the importance of consistency of making this measurement. It is a psychophysical measurement and such measurements are only valid if the subject is concentrating on the task and, particularly with children, this cannot be guaranteed. The variation in practice all revolved around how particular clinicians compensated for perceived failures in concentration by the subject. This is an area that would benefit from further research in its own right.

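### The stated comparator is glasses alone or no treatment, but every control also receives a gaming computer, so the week-6 difference estimates a different contrast unless that computer has no effect on acuity

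*Protocol article*

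**What the plan says.** The article gives several accounts of the control arm.

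- **Objectives of the study:** the efficacy question is "whether I-BiT combined with refractive correction is superior to refractive correction alone in the treatment of amblyopia".
- **Trial design, rationale:** "The choice of untreated controls was chosen as the most suitable choice for determining whether I-BiT is an effective treatment and superior to no treatment".
- **Discussion:** "We have chosen controls whose only treatment is the wearing of glasses, if indicated rather than patching".
- **Sample size** and **Statistical methods** call the comparator standard care and standard treatment respectively.
- **Trial design, what controls receive:** continued refractive adaptation or observation, and then "The participants in the control arm will also be provided with a gaming computer on which they can play games and watch DVDs". This equipment "will not have the capability to provide dichoptic stimulation nor provide eye-tracking".

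Both Trial design and Primary outcome time the week-6 endpoint from receipt of either I-BiT Plus or a laptop, which is presumably the control computer. It is thus part of the control condition as planned. No section says why it is supplied or how it fits with controls being untreated.

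The Background reports the group's earlier randomised trial, in which every arm improved by 0.07 logMAR and "there was no difference between the arms including the control (playing the videogame under non-dichoptic conditions").

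**The concern.** A randomised comparison estimates the difference between what the two arms are actually offered. Here the control offer includes home screen play and viewing, while the objective and the rationale name a control without it. The two contrasts need not be equal.

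At stake is how the primary clinical endpoint may be read in all three patient groups. If ordinary gaming or viewing had some benefit, both arms could improve through it and the difference would shrink. A null result reported in the words of the objective would then say that I-BiT is no better than glasses alone or no treatment, and this design cannot show that.

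**Working it through.** **1. Stated and delivered contrasts.** Define, for change in acuity to week 6 (positive = improvement):

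- R = mean change with glasses or observation alone
- B = effect of the I-BiT home package over R (the stated target)
- g = effect of the control computer over R

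Then:

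- I-BiT arm: R + B
- control arm: R + g
- week-6 difference: (R + B) − (R + g) = B − g

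The difference equals B only if g = 0. If g is positive, it understates B. An observed difference of zero points to B = g, not to B = 0. Adjusting for baseline acuity, age and centre, as Statistical methods plans, does not change this, because every control is offered the computer and g cannot be separated from R within the trial.

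**2. What the article says about g.** It gives no value. The nearest figure is the 0.07 logMAR gain in every arm of the earlier trial (Background). For that trial's control arm, R + g = 0.07. If neither part is negative, g lies between 0 (none of the gain due to gaming) and 0.07 (all of it). Carried over to this trial as an assumption, the stated and estimated contrasts would differ by 0 to 0.07 logMAR.

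**3. What a non-zero g would do: an illustration.** Inputs from Sample size: 20 per arm, difference 0.10 logMAR, SD 0.15, 5% significance, 80% power claimed.

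Power (two-sided, normal approximation) = Φ(difference / (SD × √(2/n)) − 1.96).

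The plan's own case first: SD × √(2/20) = 0.15 × 0.3162 = 0.0474; 0.10 / 0.0474 = 2.108; Φ(2.108 − 1.96) = Φ(0.148) = 56%. The claimed 80% is not reproduced (68% one-sided). That is a separate matter and carries no weight here.

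Now suppose B = 0.10, so that the trial measures 0.10 − g:

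| Assumed g | Measured contrast | Power, 20 per arm, SD 0.15 | n per arm for 80% |
|---|---|---|---|
| 0 | 0.100 | 56% | 36 |
| 0.02 | 0.080 | 39% | 56 |
| 0.035 | 0.065 | 28% | 84 |
| 0.05 | 0.050 | 18% | 142 |
| 0.07 | 0.030 | 9% | 393 |

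At SD 0.113, where 20 per arm does give about 80%, power falls from 80% at g = 0 to 13% at g = 0.07. Every row except the first rests on an assumed g.

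**The case against.** The strongest reply is that treatment in this article means amblyopia treatment. The Discussion sentence contrasts glasses with patching, and the control computer lacks the two features that the Background presents as the innovation. On that reading it is an inert attention control, a legitimate design, and the article discloses it openly. This softens the Discussion wording. It does not remove refractive correction alone or no treatment as the stated target of inference, and the inertness on which it depends is nowhere asserted or supported.

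Other parts of the reply stand and limit the point. Four stronger readings are tempting and are not supported:

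- **That gaming itself yields 0.07 logMAR, or 70% of the 0.1 minimum important difference (0.07 / 0.10).** The 0.07 is a total within-arm change, whereas 0.1 is a between-arm difference. Practice, regression to the mean or refractive adaptation could also produce such a gain, and the Discussion expects refractive adaptation to improve this trial's controls. The earlier trial was supervised in hospital with about 3 hours of treatment; here no control use is prescribed. The controls are similar in type, not the same.
- **That the comparison isolates the dichoptic, eye-tracked component.** I-BiT has its own games, programmes, session limits and face verification, and the control equipment is not described as matching them. The contrast is package against computer.
- **That a wrong comparator or effect estimate will pass into the definitive trial.** No comparator is stated for it. Sample size carries forward the SD, and the Discussion carries forward compliance.
- **That control use goes unrecorded.** Week-6 assessment says the machine logs its use and does not restrict this to I-BiT machines.

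**Conclusion.** The point holds as an unreconciled mismatch between the stated comparator and the control actually supplied. It should be fixed, but it is not a fatal flaw: this is a feasibility study that seeks only some indication of efficacy, and a non-dichoptic computer control is a sound choice once it is named.

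The week-6 difference estimates I-BiT at home against a non-dichoptic gaming computer, each added to glasses or observation. Its gap from the stated contrast is g, which the article does not give. The range of 0 to 0.07 logMAR assumes that g is not negative, that it does not exceed the whole control-arm gain of the earlier trial, and that the figure carries over from a supervised hospital setting to home use. The lower end, no gap at all, is not excluded.

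The consequence is mainly for a null result, which would not show that I-BiT fails to beat glasses alone or no treatment. A positive result would, if g is not negative, understate rather than overstate the effect over glasses alone.

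**What to change.** - State one comparator in Objectives of the study, Trial design, Sample size, Statistical methods and Discussion: I-BiT versus a non-dichoptic gaming computer, both with refractive correction where indicated or observation. Use it in place of the descriptions of controls as untreated, on glasses only, or on standard care or treatment.
- Limit the efficacy conclusion to that contrast, and say that a null result does not establish that I-BiT is no better than glasses alone or no treatment.
- Confirm that the usage logging in Week-6 assessment also covers the control computers, and report control hours beside I-BiT hours so that the difference can be read against screen exposure in both arms.

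The cost is some wording, plus a usage log on the control machines if they do not already keep one. The downside is a narrower claim. Design, enrolment, randomisation and the analysis model are unchanged.

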**Fig. 1 Fig1:**
[figure not shown]
Summary of trial design

### Eligibility criteria

These are summarised in Table 1.

**Table 1 Tab1:** Table of inclusion and exclusion criteria for the three groups in the clinical trial

Group 1	Group 2	Group 3
Anisometropic amblyopia	Strabismic or mixed amblyopia	Post-strabismus surgery
Inclusion criteria		
3.5^5^–12^4^ years	3.5^5^–12^4^ years	3.5^5^–12^4^
Vision in amblyopic eye between 0.3 and 1.3 logMAR with an intraocular difference of 0.2 logMAR or more	Vision in amblyopic eye between 0.3 and 1.3 logMAR with an intraocular difference of 0.2 logMAR or more	Vision in amblyopic eye between 0.3 and 1.3 logMAR with an intraocular difference of 0.2 logMAR or more
May have a manifest squint of less than or equal to 10 prism dioptres	Manifest squint must be greater than 10 prism dioptres	Residual squint following surgery (no more than 4 weeks prior) of any size
Undergone refractive adaptation^1^	Undergone refractive adaptation (if indicated)^1,2^	Undergone refractive adaptation (if indicated) ^1,2^
No previous patching or penalisation	Previous patching or penalisation acceptable	Previous patching or penalisation acceptable
No previous strabismus surgery	No previous strabismus surgery	Treatment to start within 4 weeks of strabismus surgery but no previous strabismus surgery
Can use I-BiT Plus	Can use I-BiT Plus	Can use I-BiT Plus
Exclusion criteria		
Deprivational amblyopia		
Presence of manifest nystagmus		
Other ocular or neurological disease affecting the visual system^3^		
Parent, guardian or child not prepared to give consent		

^1^Refractive adaptation is wearing refractive correction for a minimum of 12 weeks

^2^Refractive adaptation is indicated if there is a significant refractive error

^3^These include Down’s syndrome, developmental delay, craniofacial syndrome, foetal alcohol syndrome and cerebral palsy among other conditions

^4^The upper limit of the age range is 1 day before their 13th birthday

^5^The lower limit of the age range is 182 days after their third birthday

